### 7. Data Monitoring Committee

| The data monitoring committee will comprise of the Chief Investigator, co-investigators the research nurse/fellow and the statistician and will meet 2 weekly during the initial months of the recruitment phase and subsequently 4 weekly to assess progress with recruitment, data collection, data entry, loss to follow-up rates and interim analyses. |
| --- |

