Effective contraception will be defined as regular and consistent use of oral contraceptive pills/patches/vaginal ring (Nuvaring®)/ injectable contraception/ intrauterine contraception or the contraceptive implant. Use of barrier contraception or other methods such as withdrawal methods or natural family planning will not be considered as effective contraception due to their higher relative failure rate.

At 6 months post-abortion, the Research nurse/Fellow will contact patients in both intervention and control arms to assess contraceptive uptake and continuation. Data will be collected using a standardized questionnaire (Appendix 2: Topic Guide E) to explore factors that could have potentially influenced contraceptive decision-making, compliance and continuation. Information will also be obtained about the number of contacts patients in both groups have had with Health Care professionals relating to contraception since their abortion.

- **Repeat abortion at 1 and 2 years**

Anonymised data using unique patient identifiers such as Date of Birth and post code will be used to identify the proportion of study participants in each arm undergoing a repeat abortion within 1 year and 2 years following their abortion. This data will be obtained from the data routinely collected by the Public Health Department in Lambeth from the three abortion provider units for Lambeth, Southwark and Lewisham. It is possible that a small proportion of the study participants may have moved outside the boroughs of Lambeth, Southwark and Lewisham over a period of 2 years following their abortion and may have presented elsewhere for their repeat abortion. The Department of Health routinely collects statutory data returns from all abortion providers in England and Wales on all legal abortions. We will attempt to obtain permission from the Department of Health for Data linkage with the national abortion dataset for more complete information on repeat abortion rates in our study participants.

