### 6 Statistics

### 6.1 Sample Size

| A stratified design, which divides the sample among 6 strata (3 centres, 2 arms in each centre), is analyzed using the two-sided, Cochran-Mantel-Haenszel test. Sample sizes, summed across all strata, of 223 in intervention group and 223 in control group achieve 95% power and 0.05 significance to detect a difference of 15% in the percentage of women using LARC (Long- acting methods of reversible contraception such as injectables, implant or intrauterine device) or contraceptive pills in each group at 6 month follow-up. Allowing for 65% accepted participation rate and 60% follow-up rate, we require a total of 1144 patients across the three centres: 618 patients from BPAS, 366 from MSI and 160 patients from King’s College Hospital.    **Randomisation**: centre-stratified block randomization  **Primary outcome:** contraceptive uptake at 6months  **Secondary outcome:** repeat abortion rate at 1 year and 2 years  **Sample size calculation:**  Based on abortion data for Lambeth, Southwark and Lewisham residents in 2009, there were 2885 NHS abortions in BPAS, 1725 in MSI and 748 in King’s College Hospital. From this data, we can deduce the average of number of abortions at 3 months as: 721 (54%) abortions in BPAS, in 431 (32%) MSI and 187 (14%) in Kings with a total number of abortions for all the 3 centres estimated as 1339. It is anticipated that recruitment could be completed in 4-6 months.  Based on published papers (Schunmann et. Al [21]), there was 68% uptake of LARC or contraceptive pills at 4months following abortion; we have assumed the same at 6months post-abortion. 34.84% refused to participate in the above study; We have used 35 % refusal to participate for sample size calculation. There was 61.5% follow-up rate at 4months in the above study. We have used 60 % follow-up rates at 6 months. |
| --- |

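### Section 7 gives interim analyses to a committee of trial staff that includes the unblinded primary-outcome interviewer, while the design reserves no alpha for interim looks

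*Protocol*

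**What the plan says.** On membership, section 7 states: "The data monitoring committee will comprise of the Chief Investigator, co-investigators the research nurse/fellow and the statistician". No independent member is listed. The committee "will meet 2 weekly during the initial months of the recruitment phase and subsequently 4 weekly", and its task is "to assess progress with recruitment, data collection, data entry, loss to follow-up rates and interim analyses". The section does not say which endpoint the interim analyses concern, whether they are by arm or pooled, or what could follow from them.

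On the primary outcome, section 4 (study end points) states: "At 6 months post-abortion, the Research nurse/Fellow will contact patients in both intervention and control arms to assess contraceptive uptake and continuation". The nurse/fellow also arranges the 2-4 week appointment (sections 2.2 and 2.3) and makes the 3-month support call, in the intervention arm only (section 4.6).

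On the design, section 6.1 has a sample that "is analyzed using the two-sided, Cochran-Mantel-Haenszel test", with sample sizes "of 223 in intervention group and 223 in control group" that "achieve 95% power and 0.05 significance to detect a difference of 15" percentage points. Section 6.3 gives the same centre-adjusted test for the primary outcome and mentions no interim look.

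**The concern.** Two matters are at stake.

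The first is conduct. The primary outcome is a woman's own account, by telephone, of which method she uses and whether she uses it regularly. An interviewer who knows the allocation and also knows which arm is ahead can, without intending it, probe differently or try harder to reach some participants than others. Planned follow-up is only 60%, so there is much room for uneven tracing. The same committee reviews loss to follow-up, so attrition and emerging results could be seen together by the people doing the tracing.

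The second is the error rate. A design that puts the whole 0.05 on one final test has nothing left for earlier tests. If accumulating comparisons were tested and acted on, the stated 0.05 would no longer be the true error rate.

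The number of looks and the boundaries could properly be left to a statistical analysis plan, so their absence is not the point. The point is that the protocol itself fixes who receives the interim analyses.

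**Working it through.** **1. Is the stated sample size a single-test design?** Inputs from section 6.1: control rate 0.68, difference 0.15 (so 0.83 if the intervention is better), two-sided alpha 0.05, power 0.95.

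- Mean rate p = (0.68 + 0.83)/2 = 0.755.
- n per arm = [1.960 × √(2 × 0.755 × 0.245) + 1.645 × √(0.68 × 0.32 + 0.83 × 0.17)]² / 0.15² = [1.960 × 0.6082 + 1.645 × 0.5989]² / 0.0225 = 210.7, so 211.
- With continuity correction: (210.7/4) × [1 + √(1 + 4/(210.7 × 0.15))]² = 223.8, so 224 rounded up. The plan states 223.
- Power at 223 per arm without the correction: Φ[(0.15 × √223 − 1.960 × 0.6082)/0.5989] = Φ(1.75) = 0.96. The plan states 0.95.
- Gross total: 446/(0.65 × 0.60) = 1143.6, so 1144, as stated.

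The figures reproduce, to within one participant per arm, with the full 0.05 spent once. No alpha is held back.

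**2. How many participants depend on tracing?** 1144 × 0.65 = 744 recruited and 744 × 0.60 = 446 with an outcome. About 298 (744 − 446) are expected to have none.

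**3. How many meetings could see primary-outcome data?** Recruitment is expected to take 4-6 months (section 6.1) and the outcome is read 6 months after abortion. The 2-weekly meetings of early recruitment therefore precede any primary outcome. If follow-up interviews arrive over a similar 4-6 months and 4-weekly meetings continue (an assumption; section 7 does not say), the number of meetings is 4 × 30.44/28 = 4.3 to 6 × 30.44/28 = 6.5, or about 4 to 7 looks including the last.

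**4. Worst-case type I error.** Assume each look is a by-arm test of the primary outcome, rejecting when |Z| > 1.96 and acting on it, with equally spaced looks. From 400,000 simulated null trials:

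| Looks | Overall two-sided type I error |
|---|---|
| 1 | 0.050 |
| 4 | 0.127 |
| 5 | 0.141 |
| 6 | 0.155 |
| 7 | 0.167 |

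If the looks are pooled or descriptive, the error stays at 0.05.

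**5. Cost of proper boundaries, if looks are wanted.** Power is at the final look alone, with 223 per arm and 68% against 83%; overall power is at least this.

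| Looks | O'Brien-Fleming: final nominal alpha | Power | Pocock: nominal alpha per look | Power |
|---|---|---|---|---|
| 2 | 0.048 | 0.958 | 0.029 | 0.936 |
| 3 | 0.045 | 0.956 | 0.022 | 0.921 |
| 5 | 0.041 | 0.952 | 0.016 | 0.901 |
| 6 | 0.040 | 0.951 | 0.014 | 0.894 |

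**The case against.** In the plan's favour, it can be said that interim analyses come last in a list of operational items and may mean no more than pooled progress tables. Section 7 does not say that they compare arms, concern the primary outcome, involve a significance test or lead to any decision. Timing helps too: on the planned schedule recruitment is over at about the time the first 6-month outcomes arrive, so stopping or altering recruitment on primary results would need recruitment to overrun. Further, the main consultation is given by a Specialist, who is not listed on the committee, and the endpoint is defined by named methods rather than by an open rating.

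Most of this stands, and it rules out three stronger readings that a reader might infer:

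- *That the committee unblinds the assessors.* The nurse/fellow was never blinded: the same role arranges the intervention appointment and makes the intervention-arm support call. Section 3.4 conceals the allocation sequence; it does not promise a masked 6-month interview.
- *That type I error is inflated as a matter of fact.* It is inflated only under the conditions in step 4, and the protocol states none of them.
- *That outcomes are analysed every 2 to 4 weeks.* That is the meeting interval, and the early meetings have no primary outcomes to see.

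What the objection does not meet is the combination of membership and remit. The text permits by-arm results to reach the outcome interviewer and the investigators. Since the interviewer is already unblinded, keeping emerging results from that person is one of the few safeguards left.

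**Conclusion.** The point holds in this limited form. Section 7 gives undefined interim analyses to a non-independent committee that includes the person who collects the self-reported primary outcome in both arms, within a design that spends 0.05 once.

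The main consequence is a possible bias in tracing and in eliciting outcomes. The documents give no means of putting a figure on it, but with about 298 of 744 participants expected to have no outcome the opportunity is substantial.

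The effect on type I error is conditional: 5% if the looks are pooled or descriptive, and about 13% to 17% at worst. The upper figures assume 4-weekly meetings throughout outcome accrual, equal spacing, a by-arm primary test at 0.05 each time, and action on significance.

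**What to change.** In section 7, strike interim analyses from the committee's remit. Limit what it sees to pooled figures, not split by arm, on recruitment, data entry and follow-up. Add a sentence that nobody except the statistician tabulates outcome data by arm before the 6-month data are locked.

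If by-arm interim looks are really intended, state their purpose, number and timing. Restrict them to people independent of recruitment, intervention delivery and outcome collection, and place them under a stated alpha-spending boundary. An O'Brien-Fleming type boundary leaves power at about 0.95 with the present 223 per arm for up to 6 looks.

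The cost of the first option is one paragraph of wording, and investigators lose early sight of results by arm. The plan attaches no decision to those results, so the loss is small. The second option also needs independent readers to be found. Renaming the group as a trial management group would describe it better but is optional.

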### 8. Direct Access to Source Data and Documents

| The Investigator(s) will permit trial-related monitoring, audits, REC review, and regulatory inspections (where appropriate) by providing direct access to source data and other relevant documents. |
| --- |

### 9. Ethics & Regulatory Approvals

| The trial will be conducted in compliance with the principles of the Declaration of Helsinki (1996), the principles of GCP and in accordance with all applicable regulatory requirements including but not limited to the Research Governance Framework and the Medicines for Human Use (Clinical Trial) Regulations 2004, as amended in 2006 and any subsequent amendments.  This protocol and related documents will be submitted for review to King’s College Hospital Research Ethics Committee (REC) and Ethics committees of British Pregnancy Advisory Service and Marie Stopes International.  Annual progress and safety reports and a final report at conclusion of the trial will be submitted to the REC. |
| --- |

### 10. Quality Assurance

| Monitoring of this study to ensure compliance with Good Clinical Practice and scientific integrity will be managed and oversight retained by the Sexual Health and HIV Research Governance team at King’s College Hospital. |
| --- |

### 11. Data Handling

| The Chief Investigator will act as custodian for the research data.  Patients will be given unique identifiers on entry to the study. To enable us to follow them up at 1 and 2 years to examine the repeat abortion rate without having to re-contact the patient, routinely collected data from the Public Health Department in Lambeth and the Department of Health will be matched to our research data using initials, date of birth and post codes. The link between the unique patient identifier and patient details will be maintained within a secure password protected NHS database, using all current guidelines employed by King’s College NHS Foundation Trust. Only NHS encrypted memory sticks will be used for data transfer. Once the database is locked at the end of the study period (3 years) all links will be destroyed by removing initials, dates of birth and postcodes from the study data. |
| --- |

### 12. Publication Policy

| It is intended that the results of the study will be disseminated through publication in peer-reviewed scientific journals and presented at national and international conferences. |
| --- |

### 13. Financial Aspects

| Funding to conduct the research study is provided by the London Sexual Health Programme. |
| --- |

**15. Appendices**

**15.2 Appendix 2: Topic Guides for data collection**

1. **Topic Guide for baseline data collection at recruitment**: (This will be collected for both the ‘Control’ and ‘Intervention’ groups)

- Date of Birth
- Ethnicity
- Post code
- Educational achievement
- Marital/Relationship status
- Parity
- Previous abortions
- Contraceptive use immediately prior to current pregnancy
- Planned method of contraception after abortion
- Who referred for the abortion : Self/GP/Family Planning or Sexual Health clinic/other

1. **Topic Guide for Data collection at the 2-4 week consultation with the Specialist in Reproductive and Sexual Health:** (This is for the ‘Intervention’ Group only)

- Any change in the relationship status
- Whether accompanied by partner for this visit (if having a face-face consultation in a clinic)
- Smoking
- Alcohol use
- Drug misuse
- Domestic violence
- Relevant Medical History
- Any physical problems following the abortion
- Level of psychological distress following abortion
- Any additional psychological support required
- Any concerns about future fertility
- Any unprotected sexual intercourse since the last abortion
- Any use of Emergency contraception since the last abortion
- Contraceptive method provided at the time of abortion
- Current method of contraception
- When was the method started
- Is the contraceptive method being effectively used
- Any side-effects from the contraceptive method
- Any particular method of contraception medically contraindicated
- Previous contraceptive use
- Any problems with previous contraceptive methods
- Any particular contraceptive method/s unacceptable to the patient
- Attitude to future unplanned pregnancy
- Awareness of safer sex practice, STIs
- Contraceptive method provided at this visit
- Arrangements for Follow up
- Any referral to other agencies/other Healthcare professionals:
- Social services
- Safeguarding children team
- Safeguarding adults team
- Domestic violence support
- Alcohol and Drug misuse
- Mental Health team
- Psychologist
- Health advisor/counsellor
- Haven
- Services for trafficked women
- Support services for women working in prostitution
- General Practitioner

1. **Topic Guide for the phone call to study participants who DNA the 2-4 week appointment** (This is for the Intervention group only)

- Reason for DNA
- Offer suitable alternative appointment (telephone consultation or face-face clinic appointment) as preferred by the patient
- Telephone assessment (as in Section B) if willing
- Telephone Intervention purely focussed on facilitating contraceptive uptake if not willing for all the details in Section B
- Link with other Health Care professional as necessary

1. **Topic Guide for the phone call to study participants at 3 months post abortion** (This is for the intervention group only)

- Change in the relationship status
- Contact with GP or contraception service for contraceptive advice between the 2 week appointment and now
- Current method of contraception
- When was the method started
- Is the contraceptive method being effectively used
- Any side-effects from the contraceptive method
- Any unprotected sexual intercourse since the recent abortion
- Any use of Emergency contraception since the recent abortion
- Any further support required
- Arrangements for follow up

1. **Topic Guide for the phone call to study participants at 6 months post abortion** (This is for both the ‘Intervention’ and ‘Control’ group)

- Any change in the Relationship status
- Current method of contraception
- When was the method started
- Is the contraceptive method being effectively used
- Patient satisfaction with the contraceptive method
- Any unprotected sexual intercourse since the recent abortion
- Any use of Emergency contraception since the last abortion
- Any contact with GP/contraception service for contraceptive advice between the abortion and now
- Pregnancy intentions for the next 1 and 2 years
- Attitude to future unplanned pregnancy
- Alcohol use
- Drug misuse
- Domestic (Intimate partner) violence

______________________________________________________________________________________
